#### Interventions, modifications, adherence, and concomitant care

The assigned intervention will be discontinued only in response to participant’s request. No intervention modification is planned during the trial. Adherence to interventions mainly refers to participant self-management adherence. No concomitant care or interventions are permitted during this trial.

#### Plans for collection, laboratory evaluation, and storage of biological specimens for genetic or molecular analysis in this trial/future use

We have no plans to collect or store biological specimens involved in this trial.

#### Outcome measures

Primary outcome measures

The primary outcome is the success rate of remimazolam tosylate for sedation for diagnosis and treatment during upper gastrointestinal endoscopy. Success is defined by a composite measure (all three conditions must be met) of the following:Completion of the procedure of upper gastrointestinal endoscopy.No requirement for rescue sedative medication.After administering the initial dose of the trial drug, additional administration is ≤2 times within any 5-min period.

Secondary outcome measures

The secondary outcomes are as follows:The induction time of sedation: defined as the time interval from the initial administration of the trial drug to the first MOAA/S score of ≤2.The time of full alertness: defined as the time from the discontinuation of sedative medication to full alertness (the first of three consecutive MOAA/S scores of 5).The incidence of drug injection pain.Digestive endoscopist and participant satisfaction, measured on a scale from 1 to 10. Endoscopists and participants will score their satisfaction with the scale, with 1–3 (dissatisfied), 4–6 (satisfied), or 7–10 (very satisfied), after upper gastrointestinal endoscopy.The time of discharge: defined as the time interval from the termination of the administration of the trial drug to meeting the discharge criteria (modified postanesthesia discharge scoring system score of ≥9, with two points in the vital sign item).The incidence of hypoxia during sedation: defined as 75% ≤ SpO_2_ < 90% for <60 s.All adverse events occurring during the procedure were recorded using tools proposed by the World Society of Intravenous Anesthesia (SIVA)’s International Sedation Task Force [19].

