### Aims and objectives

Compared with propofol, the safety and efficacy of remimazolam tosylate during upper gastrointestinal endoscopy are verified based on the completion of upper gastrointestinal endoscopy, vital signs of participants, and satisfaction of endoscopists and patients.

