^l^“Minor” adverse events are those encountered periodically in most sedation settings and that pose little threat given appropriate sedationist skills and monitoring.

^m^“Minimal” adverse events are those that alone present no danger of permanent harm to the patient

All participants will receive 10 g of 2% lidocaine hydrochloride mucilage. They will be administered supplemental oxygen (3–4 L/min) before injecting sufentanil until the participants are fully alert after the procedure. Approximately 1 min after administering 5 μg of sufentanil, remimazolam tosylate 0.15 mg/kg, remimazolam tosylate 0.2 mg/kg, or propofol 1.5 mg/kg will be used to induce sedation. If the MOAA/S score is ≤2, upper gastrointestinal endoscope intubation will be initiated. If the MOAA/S score is still >2 after two min or if the upper gastrointestinal endoscopy attempt fails because the participant is writhing or nauseating, the experimental group will be given remimazolam tosylate (0.05 mg/kg) and the control group will be given propofol (0.5 mg/kg). The administration time is 10 s, and the interval between each supplementation dose is at least 1 min. After the endoscope intubation, to maintain a certain degree of sedation (MOAA/S score, ≤2), additional remimazolam tosylate or propofol will be administered as necessary. If two doses (after the initial dose) within any 5-min window are not sufficient to obtain or maintain adequate sedation, the case will be designated a treatment failure and rescue sedative medication (propofol) will be administered to obtain or maintain adequate sedation to complete upper gastrointestinal endoscopy.

Participants may have perioperative respiratory-related adverse events during upper gastrointestinal endoscopy. If the SpO_2_ is <95%, we will lift the patient’s mandible. If it is <90%, we will increase the oxygen flow of the nasal catheter to 6 L/min. If the SpO_2_ is still <90%, we will suspend the procedure, pull out the upper gastrointestinal endoscope, and perform positive pressure ventilation with a mask. If it still cannot be corrected, laryngeal mask airway or tracheal intubation will be performed to control breathing. During the procedure, participants with hypotension or bradycardia will be administered ephedrine or atropine, as appropriate.

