#### Allocation masking

This study follows a single-blinded method. All participants are blinded to the assignment of the trial (the injection site will be shielded) and will be randomly assigned to any of the three groups.

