##### Statistical analysis plan

All statistical analyses in this experiment will be programmed and calculated using the SAS analytics software version 9.4. In this study, the noninferiority one-sided test used for the main efficacy outcome is that a *P*-value of ≤0.0125 will be considered statistically significant. All other tests will be two-sided tests, with a *P*-value of ≤0.05 considered statistically significant, and the confidence interval will be set at 95%.

Measurement of basic data in different treatment groups will be statistically expressed as mean ± standard deviation or median (interquartile range [IQR]).

The *χ*^2^ test will be used for the success rate of sedation, incidence of injection pain, hypoxia, and adverse events. The analysis of variance will be used to induce time of sedation, full alertness, and discharge. The rank sum test will be used for calculating the satisfaction of endoscopists and participants.

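### The endoscopist's satisfaction score is a secondary outcome named in the aims, but nothing in the masking plan protects it from expectation bias

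*Protocol article*

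**What the plan says.** - **Aims and objectives** (Protocol article) lists what the comparison with propofol rests on. Besides completion of the endoscopy, it names "vital signs of participants, and satisfaction of endoscopists and patients".
- **Outcome measures** makes satisfaction a secondary outcome with two raters: "Digestive endoscopist and participant satisfaction, measured on a scale from 1 to 10". The score is given after the procedure and carries verbal labels: "with 1–3 (dissatisfied), 4–6 (satisfied), or 7–10 (very satisfied), after upper gastrointestinal endoscopy".
- **Allocation masking** states the level of blinding, "This study follows a single-blinded method", and whom it covers: "All participants are blinded to the assignment of the trial (the injection site will be shielded". The endoscopist is not mentioned there, and no other section masks the endoscopist.
- **Statistical analysis plan** (a subsection of the article) says: "The rank sum test will be used for calculating the satisfaction of endoscopists and participants". For everything except the main efficacy outcome, "All other tests will be two-sided tests, with a *P*-value of ≤0.05 considered statistically significant".

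**The concern.** A 1 to 10 satisfaction rating is a judgment, and its value depends on the rater not knowing the treatment. Here two people rate on the same scale. One is blinded by design. For the other, the plan states no masking of the drug, the syringe or the allocation.

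If endoscopists know which patients received the new drug, their scores may reflect what they expect of it as well as how the procedure went. A difference between arms, or its absence, could not then be attributed to the drug. The aims place endoscopist satisfaction among the bases for judging remimazolam tosylate against propofol, so the score is likely to be read as evidence. What is at stake is the interpretation of that one secondary measure.

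**Working it through.** **1. Who rates, and who is masked**

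| Rater | Scores satisfaction (Outcome measures) | Stated to be blinded (Allocation masking) |
|---|---|---|
| Participant | Yes, 1 to 10 | Yes, with the injection site shielded |
| Endoscopist | Yes, 1 to 10 | Not mentioned |

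The gap concerns one of two raters. The protocol has no power statement for satisfaction, so there is no stated figure to reproduce.

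**2. How small a scoring shift would matter**

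A significance test cannot tell a shift caused by expectation from one caused by the drug. The question is how large a shift would show up as a difference.

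Inputs:
- From Sample size: 600 per arm and 10% dropout, so 600 × 0.90 = 540 evaluable per arm.
- From the Statistical analysis plan subsection: two-sided 0.05.
- Assumed, because the document gives none: standard deviation (SD), mean score, size of shift, and a pairwise comparison of two arms.

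Normal approximation: the standard error of a difference in means is SD × √(2/540) = SD × 0.0609. The shift that just reaches significance is 1.96 times this.

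| Assumed SD | Standard error | Shift that just reaches p = 0.05 |
|---|---|---|
| 1.0 | 0.061 | 0.12 points |
| 1.5 | 0.091 | 0.18 points |
| 2.0 | 0.122 | 0.24 points |

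For SD 1.5 and a shift of 0.3 points, 0.3 / 0.0913 = 3.29, and the chance of rejection is about Φ(3.29 − 1.96) = Φ(1.33) ≈ 0.91.

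A simulation of the rank sum test agrees (400 runs per setting, 540 per arm, rounded normal scores limited to 1–10, SD 1.5, shift 0.3):

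| Assumed mean | Rejection, 1–10 score | Rejection, three bands |
|---|---|---|
| 5.5 | 89% | 83% |
| 7 | 90% | 75% |
| 8 | 87% | 61% |
| 8.5 | 90% | 49% |
| 9 | 84% | 32% |

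With no shift, rejection was 5–7% on the score and 3–8% on the bands. The middle column gives the 84% to 90%: in a trial this large, a shift of a few tenths of a point in an unmasked rater's scores would usually be declared significant. This shows sensitivity. It does not show that such a shift will occur, or in which direction.

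**3. The verbal bands**

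The bands hold 3, 3 and 4 of the ten points. Scores 4 and 5 lie below the midpoint of 5.5 but are labelled satisfied, and seven of ten points carry a favourable label. The same labels apply in every arm, so they cannot create a difference between arms. They can still show one: for assumed means of 7.0 and 6.7 (SD 1.5), the share labelled very satisfied is about 63% against 55%.

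The last column of the simulation matters only if bands are ranked instead of scores. The loss is then small at a mid-scale mean (89% to 83%) and large near the ceiling (84% to 32%).

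**The case against.** The strongest reply is that the design is declared openly. A single-blind trial does not promise to mask the endoscopist, and nowhere is the endoscopist said to see the injection or know the arm. The shield at the injection site may already block the endoscopist's view. Blinded participants rate on the same scale, the outcome is secondary, and the noninferiority test does not use it.

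Most of this stands as a limit on the point. An unblinded endoscopist is an inference from the single-blind label and from participants alone being named; it is not a documented fact. It does not remove the point, because the masking section does define its scope, and a subjective rating named in the aims falls outside it.

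A reader might infer more than the document supports:

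- **That the bands make every arm look favourable.** They do not: a dissatisfied band exists, the labels are common to all arms, and the top band can separate arms. Calling 4 or 5 satisfied is a labelling preference.
- **That the test is run on the bands and loses power.** The outcome is described as measured from 1 to 10, and a rank sum test fits that score. The detail is commonly left to an analysis plan, and the power loss depends on an assumed mean near the ceiling.
- **That the endoscopist's judgment also biases the primary outcome.** Procedure of the trial lets a top-up follow if the "upper gastrointestinal endoscopy attempt fails because the participant is writhing or nauseating", but it does not say who decides this.
- **That a noninferiority claim will be made for satisfaction.** None is planned; satisfaction gets an ordinary two-sided test.

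**Conclusion.** The point holds in a limited form. As written, the endoscopist's satisfaction score has no stated protection against expectation bias, although it is a secondary outcome and named in the aims. The participant score is blinded and is not affected. The noninferiority test on sedation success does not use either score.

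The size of any bias is unknown. Under assumed SDs of 1.0 to 2.0 and 540 evaluable per arm, a shift of roughly 0.12 to 0.24 points would be enough to reach p = 0.05, so trial size offers no protection. The conclusion rests on reading single-blind, with participants alone named, as leaving the endoscopist unmasked. If masking is arranged in practice, one sentence saying so closes the point. It is worth correcting because the remedy is cheap.

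**What to change.** In **Allocation masking**:

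1. Extend the existing shield so that syringe, line and injection site are hidden from the endoscopist, and keep it in place for top-up doses as well as the initial dose.
2. State that the arm is not disclosed to the endoscopist before the satisfaction score is recorded.
3. Record the endoscopist's guess of the arm with the score, so that the success of masking can be reported.

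If the endoscopist cannot be masked, say so, report that score as an unblinded assessment, and rest conclusions about satisfaction on the participant score.

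As a minor clarification, confirm in the **Statistical analysis plan** subsection that the rank sum test uses the 1 to 10 score and that the verbal bands are descriptive. The scale and labels need not change. Trial status expects recruitment from February 2021 to December 2022, and relabelling a scale already in use could make earlier and later scores hard to compare.

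Cost: a larger screen or opaque cover at five centres, one extra item on the case report form and a few sentences of text. No added staff, and no change to dosing or sample size. The downside is that masking may be imperfect, which the recorded guess would reveal. If the change comes after recruitment has begun, note its date at each centre so that scores before and after can be told apart.

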#### Methods to handle protocol nonadherence and statistical methods to handle missing data

Statistical analysis will be conducted on an intention-to-treat basis. The outcomes will be analyzed as randomized, regardless of protocol adherence. All variables will be screened for frequency and type of missingness. Multiple imputation will be used if missingness is >5% in any variable. In the case of missing data and imputation, complete case analysis will be performed as a sensitivity analysis.

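### Discharge time and full-alertness time start from different events, so for a rescued remimazolam participant the discharge clock also counts the rescue-propofol phase

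*Protocol article*

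**What the plan says.** The two recovery outcomes are defined in the same list of secondary outcomes (Outcome measures), with different starting points:

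- Full alertness: "defined as the time from the discontinuation of sedative medication to full alertness".
- Discharge: "defined as the time interval from the termination of the administration of the trial drug to meeting the discharge criteria".

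Procedure of the trial sets out what happens when sedation is inadequate. A participant in whom two top-ups inside 5 minutes do not work counts as a failure of treatment. The step that follows is stated there: "rescue sedative medication (propofol) will be administered to obtain or maintain adequate sedation to complete upper gastrointestinal endoscopy". Propofol is also the control drug.

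The protocol does not treat rescue as part of the trial drug. The Methods part of the abstract names the rescue agent separately from top-ups of the trial drug. The primary outcome likewise makes absence of rescue one condition and the number of trial-drug top-ups another.

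On attribution, the section on nonadherence and missing data says: "The outcomes will be analyzed as randomized, regardless of protocol adherence".

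**The concern.** For a participant who is never rescued, the last trial-drug dose is the last sedative dose, and the two clocks start together. They separate only when a second sedative is given. In the remimazolam arms that sedative is a different drug from the assigned one, so the two phrases point to different moments.

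Read literally, discharge time in a rescued remimazolam participant then includes time during which the participant is still being sedated. That is not recovery time, and the companion outcome excludes it. In the control arm the rescue agent is the same substance as the trial drug, and the text does not say whether a rescue dose moves the start of the clock.

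Recovery is one of the features on which remimazolam is to be compared with propofol. On the plan's own assumptions rescue occurs only in the remimazolam arms, so any distortion falls on one side of the comparison.

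**Working it through.** **1. Inputs from the protocol article.** Sample size gives 600 participants per group and assumed success of 95% in each remimazolam arm and 100% with propofol. The 600 is taken as given. That section states no noninferiority margin, so the figure cannot be rebuilt from its inputs, and nothing below depends on rebuilding it.

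**2. Effect in one participant.** Let T be the time of the last remimazolam dose, R the time of the last rescue propofol dose, and D the time the discharge criteria are met.

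- Discharge time as defined, read literally: D − T.
- Discharge time from the same starting point as full alertness: D − R.
- Difference: (D − T) − (D − R) = R − T, the lag L.

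**3. Number affected.** Failures per remimazolam arm = 600 × (1 − 0.95) = 30, or 60 over both arms. After the planned 10% dropout, 600 × 0.90 = 540 and 540 × 0.05 = 27 per arm. In control, 600 × (1 − 1.00) = 0. These are upper figures for rescue, because a failure may also be a procedure that was not completed, without rescue.

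**4. Shift in the arm mean.** Shift = rescued fraction × L. The documents give no value for L, so a range of 2 to 15 minutes is assumed.

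| Rescued fraction | L = 2 min | L = 5 min | L = 10 min | L = 15 min |
|---|---|---|---|---|
| 2% (assumed) | 0.04 | 0.10 | 0.20 | 0.30 |
| 5% (plan) | 0.10 | 0.25 | 0.50 | 0.75 |
| 10% (assumed) | 0.20 | 0.50 | 1.00 | 1.50 |

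Entries are minutes added to the mean discharge time of a remimazolam arm. The 5% row is the one that rests on the plan.

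**5. Which end of the range.** Rescue is triggered within a 5-minute window and top-ups may be as little as 1 minute apart, so the first rescue dose should follow the last remimazolam dose closely. L, however, runs to the *last* rescue dose. The upper end therefore needs rescue dosing that continues for some time. The eligibility criteria allow endoscopies of up to 30 minutes, so this is possible but unlikely to be typical.

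**6. A condition on step 2.** The literal reading assumes that remimazolam stops once rescue begins. Procedure of the trial implies this. The section on interventions, modifications, adherence and concomitant care says instead that the assigned intervention stops only if the participant asks, and it allows no concomitant interventions. The two sections do not fit together and must be reconciled.

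**The case against.** **The wording may be only loose.** Propofol is itself one of the trial's drugs. If *trial drug* is read by substance, rescue propofol counts in every arm and the mismatch disappears. If it is read by role, the discharge clock stops before rescue in every arm, and the rule is at least formally the same across arms. This is a fair reply, and it rules out any claim that the control-arm clock definitely restarts at rescue, because no section says so. It does not remove the point. The protocol separates rescue from trial drug in two places, which favours the reading by role. Under that reading the extra time arises wherever rescue occurs, which the plan expects only in the remimazolam arms.

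**The effect is small.** This stands. At the planned failure rate it is well under a minute on the arm mean, and the short interval implied by the rescue trigger favours the lower part of the range.

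**A reader might infer more: that propofol given as rescue spoils the whole secondary and safety comparison.** Hypoxia is listed as "The incidence of hypoxia during sedation" with no cut-off at rescue, and induction is "defined as the time interval from the initial administration of the trial drug to the first MOAA/S score of ≤2", whichever drug achieved it. The documents do not support calling this an error. Counting events by randomised arm gives the treatment-policy effect of starting with remimazolam and rescuing with propofol, which is a legitimate target. Analyses that separate rescued participants commonly sit in an analysis plan, and none is shown. The documents give no hypoxia rate in any arm and none after rescue, so a claimed loss of power would rest wholly on chosen inputs, and the sample size is set for the primary outcome only. Nor does the text say that injection pain is assessed at rescue doses. Scoring induction as not achieved after rescue would leave no value for the planned analysis of variance.

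**Conclusion.** The point holds for the discharge definition. Two recovery outcomes in one list have different zero points. Read literally, the discharge rule counts the rescue-propofol phase in rescued remimazolam participants, and in the control arm it is ambiguous. At the planned 95% success this touches at most 30 of 600 participants per remimazolam arm, against none expected in control, and lengthens mean discharge time by about 0.1 to 0.75 minutes. The bias is systematic and works against remimazolam.

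The size rests on three assumptions: every failure is rescued, remimazolam stops at rescue, and the lag is 2 to 15 minutes. The primary outcome is unaffected because rescue already counts as failure. The as-randomised analysis of hypoxia, injection pain and adverse events is not at fault. This is a minor but clear flaw in a definition, worth correcting because the correction costs almost nothing.

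**What to change.** 1. Define both recovery times, in all arms, from one zero point: *the last dose of any sedative, including rescue propofol*. Values for participants who are not rescued do not change.
2. Record the times of rescue doses, if this is not already done. The participant timeline says that combined drugs are recorded throughout the procedure, so the field may already exist.
3. Reconcile Procedure of the trial, which provides for rescue propofol, with the section on interventions and concomitant care, which allows no concomitant interventions and lets the assigned drug be stopped only at the participant's wish.
4. Keep the as-randomised analysis of hypoxia, injection pain and adverse events. A supplementary table that flags rescued participants, and marks induction times reached only after rescue, is optional.

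The cost is a wording change, possibly one CRF field, and the ethics committee review that the protocol requires for any change. With the common zero point, discharge time no longer reflects sedation prolonged by rescue. The need for rescue is still captured in the primary outcome.

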#### Procedure of the trial

Routine preparations are conducted before upper gastrointestinal endoscopy (generally fasting for at least 6 h preoperatively and no drinking water for at least 2 h). Before inducing sedation for upper gastrointestinal endoscopy, venous access will be established. During the procedure, peripheral oxygen saturation (SpO_2_), heart rate, continuous right upper limb noninvasive blood pressure, and Modified Observer’s Assessment of Alertness/Sedation (MOAA/S) score will be monitored. Specific monitoring indicators are presented in Table 2. Perioperative respiratory-related adverse events and participants’ treatment methods are shown in Table 3, and adverse events of anesthesia and sedation are shown in Table 4.

**Table 2 Tab2:** The specific monitoring indicators

Monitoring indicators	Stage	Monitoring frequency
SpO_2_, heart rate, blood pressure, MOAA/S score	Before beginning sedation induction	After taking lidocaine hydrochloride mucilage and entering the room, the patient is placed in the left decubitus position on the examination bed, and indicators are recorded:
	Sedation induction started when fully awake	(1) The initial dose of remimazolam or propofol is intravenously administered (this time will be recorded as 0 min) (2) Within 1 min after the initial intravenous dose (3) When the upper gastrointestinal endoscope is successfully inserted (4) After successfully inserting the upper gastrointestinal endoscope, every 3 min until the end of upper gastrointestinal endoscopy (5) At the end of upper gastrointestinal endoscopy (6) When the patient is fully alert (MOAA/S score of 5 points for three consecutive times; for an MOAA/S score of 5, it should reach 5 the next two times).

**Table 3 Tab3:** Perioperative respiratory-related adverse events and treatment records

SpO_2_ before the procedure (no oxygen)		Lowest SpO_2_ during the procedure		Is SpO_2_ <90% during the procedure?	Yes □ No□
Duration of SpO_2_ <90%		Did oxygen flow increase during the procedure?	Yes □ No □	Is the patient's mandible lifted?	Yes □ No□
Is mask ventilation required?	Yes□ No□			Is endotracheal intubation performed?	Yes □ No □

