Treatment of respiratory-related adverse events: When SpO_2_ is <95%, the participant will be lifted to the mandible. If SpO_2_ is <90%, the oxygen flow of the nasal catheter will be increased to 6L/min. If SpO_2_ is still <90%, the procedure will be stopped, the upper gastrointestinal endoscope will be pulled out, and positive pressure ventilation will be performed using a mask. If SpO_2_ cannot be corrected, laryngeal mask airway or tracheal intubation will be performed to control breathing

**Table 4 Tab4:** Adverse events of anesthesia and sedation

Step 1: Was there one or more adverse events associated with this sedation encounter?				
No, this form is now complete.	Yes, fill out remainder of form below.			
Step 2: Please DESCRIBE the adverse events(s). Check all that apply.				
Minimal risk descriptors	Minor risk descriptors		Sentinel risk descriptors	
Vomiting/Retching	Oxygen desaturation (75–90%) for <60s		Oxygen desaturation, severe (<75% at any time) or prolonged (<90% for >60s)	Other, specify below
Subclinical respiratory depression^a^	Apnea, not prolonged		Apnea, prolonged (>60 s)	
Muscle rigidity, myoclonus	Airway obstruction		Cardiovascular collapse/shock^g^	
Hypersalivation	Failed sedation^e^		Cardiac arrest/absent pulse	
Paradoxical response^b^	Allergic reaction without anaphylaxis			
Recovery agitation^c^	Bradycardia^f^			
Prolonged recovery^d^	Tachycardia^f^			
	Hypotension^f^			
	Hypertension^f^			
	Seizure			
Step 3: Please note the INTERVENTIONS performed to treat the adverse events(s). Check all that apply.				
Minimal risk	Minor risk	Moderate risk	Sentinel intervention	
No intervention performed	Airway repositioning	Bag valve mask-assisted ventilation	Chest compressions	Other, specify below
Administration of:	Tactile stimulation	Laryngeal mask airway	Tracheal intubation	
Additional sedative(s)	or the administration of:	Oral/nasal airway	or the administration of:	
Antiemetic	Supplemental oxygen, new or increased	Continuous positive airway pressure (CPAP)	Neuromuscular block	
Antihistamine	Antisialogogue	or the administration of:	Pressor/epinephrine	
		Reversal agents	Atropine to treat bradycardia	
		Rapid i.v. fluids		
		Anticonvulsant i.v.		
Step 4: Please note the OUTCOME of the adverse events(s). Check all that apply.				
Minimal risk outcome	Moderate risk outcome		Sentinel outcome	
No adverse outcome	Unplanned hospitalization or escalation of care^h^		Death	Other, specify below
			Permanent neurological deficit	

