#### Sample size

In this study, the noninferiority test will be performed between the experimental and control groups (i.e., experimental group 1 vs. control group; experimental group 2 vs. control group). Assume that the success rate of sedation in the propofol group is 100% and that in each remimazolam tosylate group is 95%. Considering the first type of error, *α* = 0.0125 (single-sided), 90% power, and 10% dropout rate, 600 participants are required for each group, with a total of 1800 for the three groups.

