##### Additional analyses

Subgroup analysis: Subgroup analysis via an interaction by gender, age (18–24, 25–44, and 45–60 years), and BMI (<23 and ≥23 kg/m^2^) will be used to analyze the primary and secondary outcomes among subgroups.Safety analysis: General safety evaluations will be based on the incidence and type of adverse events. Safety variables will be tabulated and presented for all participants in the safety set. Adverse events will be coded using the World SIVA adverse sedation event reporting tool. The number (%) of participants with any adverse events will be summarized.

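### The secondary outcome named hypoxia counts only brief, mild desaturation, so its χ² test can show equal or less hypoxia in an arm whose desaturation is worse

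*Protocol article*

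**What the plan says.** Under Outcome measures, one of the secondary outcomes is "The incidence of hypoxia during sedation: defined as 75% ≤ SpO_2_ < 90% for <60 s". The range is closed at both ends: a floor on depth and a ceiling on duration.

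Table 4 (under Procedure of the trial) has two desaturation descriptors. The minor-risk one is "Oxygen desaturation (75–90%) for <60s". The sentinel-risk one is "Oxygen desaturation, severe (<75% at any time) or prolonged (<90% for >60s". The hypoxia outcome matches the first. Nothing in the article adds the second to it.

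The Statistical analysis plan section says that the χ² "test will be used for the success rate of sedation, incidence of injection pain, hypoxia, and adverse events", so hypoxia and adverse events are tested as separate items, at the two-sided 0.05 level that applies to everything except the primary test.

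Three other provisions bear on the point:
- The last secondary outcome covers adverse events as a whole: "All adverse events occurring during the procedure were recorded using tools proposed by the World Society of Intravenous Anesthesia".
- Additional analyses bases the safety evaluation on the incidence and type of adverse events and adds: "The number (%) of participants with any adverse events will be summarized".
- Table 3 asks "Is SpO_2_ <90% during the procedure" as a yes/no item and also records the lowest SpO2 and the duration below 90%.

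**The concern.** An outcome called the incidence of hypoxia should not improve when hypoxia gets worse. This one can. A participant whose single episode lasts 70 s, or reaches 70%, counts as having no hypoxia, while one with a 20 s dip to 88% counts as a case. If one drug or dose turns brief episodes into prolonged ones, its hypoxia rate goes down.

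The Abstract names cardiac and pulmonary adverse events as the primary concerns with current sedatives. The Background lists respiratory depression and hypoxia among the drawbacks of propofol, and the Discussion warns of respiratory depression from too much remimazolam tosylate. Hypoxia is the only respiratory event given its own line among the secondary outcomes, and the trial compares two remimazolam doses as well as propofol. Readers are likely to take that line as the respiratory result.

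There is also a small gap. An episode between 75% and 90% lasting exactly 60 s meets neither the outcome nor either Table 4 descriptor.

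**Working it through.** **Coverage of the definition.** Every episode below 90% falls into one of these cells:

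| Episode | Hypoxia outcome | Table 4 |
|---|---|---|
| 75% to <90%, under 60 s | counted | minor |
| 75% to <90%, exactly 60 s | not counted | neither row |
| 75% to <90%, over 60 s | not counted | sentinel |
| Below 75%, any duration | not counted | sentinel |

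The article does not say how to class a participant who has both a qualifying brief episode and a severe one. If any qualifying episode is enough, that participant counts. The participants certainly missed are those whose only episodes are severe or last 60 s or longer.

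**Illustration.** The plan states no hypoxia rate or power, so there is no figure to reproduce. The arm size comes from Sample size ("600 participants are required for each group, with a total of 1800 for the three groups"). All event counts below are assumptions. *Brief* means participants counted by the outcome, and *severe* means participants with SpO2 <90% whom the outcome misses, so the two do not overlap. Each comparison is between two arms.

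Pearson χ² without continuity correction is z², where z = (pA − pB) / √[p̄(1 − p̄)(1/600 + 1/600)] and p̄ is the pooled proportion.

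Scenario 1 for any SpO2 <90%, worked through:
- A = 60 + 6 = 66 of 600 = 11%; B = 60 + 36 = 96 of 600 = 16%.
- p̄ = 162/1200 = 0.135.
- Standard error = √(0.135 × 0.865 × 2/600) = 0.0197.
- |z| = 0.05/0.0197 = 2.53, so p = 0.011.

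The other rows use the same formula:

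| Scenario | Brief, A vs B | Severe, A vs B | Outcome as defined | Any SpO2 <90% |
|---|---|---|---|---|
| 1. Equal brief, more severe in B | 60 vs 60 | 6 vs 36 | 10% vs 10%, p=1.0 | 11% vs 16%, p=0.011 |
| 2. Same total, B shifted to severe | 48 vs 24 | 12 vs 36 | 8% vs 4%, p=0.0035 | 10% vs 10%, p=1.0 |
| 3. Few severe | 30 vs 30 | 3 vs 9 | 5% vs 5%, p=1.0 | 5.5% vs 6.5%, p=0.47 |
| 4. Severe very rare | 48 vs 54 | 1 vs 2 | 8.0% vs 9.0%, p=0.53 | 8.2% vs 9.3%, p=0.47 |

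In scenario 1 the outcome shows no difference although B is worse. In scenario 2 it significantly favours B, although B has the same overall rate below 90% and three times the severe or prolonged events (2% vs 6%, p=0.0004). In scenarios 3 and 4 the choice of definition hardly changes the conclusion.

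Scenario 2 also shows that a single any-<90% rate is not enough: it reads 10% in both arms. The severe or prolonged subcategory must be reported beside it.

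**The case against.** The strongest reply is that severe desaturation is counted, one line further down. All adverse events form a secondary outcome with its own χ² test, the form has a sentinel row for exactly these events, and they are to be reported by type. In scenario 1, the sentinel row alone would show 6 vs 36 participants: p̄ = 0.035, standard error 0.0106, |z| = 4.7, p about 2×10⁻⁶. That is far stronger than the p=0.011 from the any-<90% outcome. A reader might infer from the definition that serious hypoxia disappears from the trial or would be concealed. The documents do not support that, and this part of the reply stands.

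Three further replies have weight:
- The rates are assumed, and 6% may be high for the population in Table 1 (ASA I–II, BMI below 28, lung and heart disease excluded), all of whom receive supplemental oxygen. If severe events are rare, the two definitions nearly coincide.
- A reader might infer that every participant with a severe episode leaves the count. The article states no worst-episode rule, so that is too absolute.
- The definition has a visible logic: it takes over one tier of the reporting tool and keeps the tiers separate.

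What does not stand is that the adverse-event route repairs the hypoxia line. The stated summary of participants with any adverse event pools sentinel desaturation with events as slight as retching. Reporting by type shows the sentinel events elsewhere but leaves the tested hypoxia rate as it is. Nor is this a detail the article leaves to a fuller document: it gives an explicit numerical definition.

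**Conclusion.** The point holds for the named hypoxia outcome. As written, it is the incidence of minor desaturation under a broader label. It misses participants whose only episodes are below 75% or last 60 s or longer, and its χ² test can show no difference, or a difference in the wrong direction, when one arm desaturates more severely.

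The size cannot be fixed from the documents. Under assumed rates it runs from a reversed comparison (8% vs 4%, p=0.0035, with severe events at 2% vs 6%) to almost nothing (p=0.53 against 0.47, with 1 vs 2 severe events). These figures rest on 600 analysed per arm, two-arm comparisons, and the split between counted and missed participants set out above.

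A reader might go further and conclude that the noninferiority result is affected. It is not: the primary outcome, sedation success, contains no oxygen saturation component. This is a fault in one secondary outcome, with the underlying data still collected. It should be fixed, but the trial's main conclusion does not depend on it.

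**What to change.** Define the hypoxia outcome as any SpO2 below 90% during sedation, regardless of depth or duration. Report by arm two subcategories that together cover every event and do not overlap:
- 75% to <90% for ≤60 s;
- <75% at any time, or <90% for >60 s.

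The ≤60 s limit closes the gap at exactly 60 s. State that each participant is placed in the worse subcategory reached.

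The cost is a sentence or two in Outcome measures, settled before data are analysed by arm. No new data are needed, since Table 3 already records whether SpO2 fell below 90%, the lowest value and the duration. Table 3 words its items by the procedure while the outcome speaks of sedation, so the definition should name one observation window for both. The change concerns only how the outcome is counted and leaves clinical management untouched.
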